| Description of interventions | Arm A: Pectin fibre (15g/day) combined with 15g whey protein supplement and 5g cocoa powder reconstituted as a shake Arm B (control/placebo): Whey protein supplement (30g/day) and 5g cocoa powder reconstituted as a shake.  To validate MRI scans as a tool to assess intestinal wall thickness to indicate gut permeability on MASLD patients, our team will scan 15 healthy volunteers twice, at baseline and after 6 weeks, and then compare their results with MASLD participant results at baseline and after 6 weeks. |
| Duration of study | Duration of the study:  24 months.  Duration per participant:  Each participant will participate for 6 weeks. |
| Randomisation and blinding | The study will be a parallel design, placebo-controlled, randomised dietary intervention study in which each participant will be randomly assigned to either pectin supplementation or control dietary supplement using online software (sealedenvelope.com). |
| Outcome measures | Primary outcomes:  Quantification of blood markers associated with physiological processes and pathways contributing to systemic inflammation pathway (TNFα, IL-6, IL-10, IFNᵞ, C-Reactive Protein, Zonulin (Haptoglobulin), IL-1β).  Secondary outcomes:   1. Assessment of changes in anthropometric measures 2. Assessment of changes in general metabolic indicators, such as fasting blood glucose and other blood-based markers relevant to MASLD (e.g., CK18-M30, CK18-M65, PROC3, Enhanced Liver Fibrosis (ELF), NIS2+™, YKL-40, microRNA miR-34a-5p, liver-associated enzymes such as Alanine Aminotransferase (ALT), Aspartate Aminotransferase (AST), gamma-glutamyl transferase (GGT), Alkaline Phosphatase (ALP)), bilirubin levels, lipid profiles, and platelet counts. 3. Exploration of modifications in non-invasive physiological assessments linked to liver characteristics, such as fat content and stiffness through controlled attenuation parameter (CAP) and transient elastography. 4. Observation of alteration in fat in liver and other surrounding abdominal organs through Dixon MRI sequence in patients who will agree to have 2 MRI scans. 5. Validation of MRI measures (T2*) as a tool to measure gut permeability among MASLD patients and investigation of changes in gut permeability in participants undergoing two MRI scans. 6. Investigation the presence of gene variants such as MUC2, encoding Mucin protein, that are associated with gut permeability. |

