## SECONDARY OBJECTIVES

1. Assessment of changes in anthropometric measures.
2. Assessment of changes in general metabolic indicators, such as fasting blood glucose and other blood-based markers relevant to MASLD (e.g., CK18-M30, CK18-M65, PROC3, Enhanced Liver Fibrosis (ELF), NIS2+™, YKL-40, microRNA miR-34a-5p, liver-associated enzymes such as Alanine Aminotransferase (ALT), Aspartate Aminotransferase (AST), gamma-glutamyl transferase (GGT), Alkaline Phosphatase (ALP)), bilirubin levels, lipid profiles, and platelet counts.
3. Exploration of changes in gut microbiome composition.
4. Exploration of modifications in non-invasive physiological assessments linked to liver characteristics, such as fat content and stiffness through controlled attenuation parameter (CAP) and transient elastography.
5. Observation of alteration in fat in liver and other surrounding abdominal organs through Dixon MRI sequence in patients who will agree to have 2 MRI scans.
6. Validation of MRI measures (T2*) as a tool to measure gut permeability among MASLD patients and investigation of changes in gut permeability in participants undergoing two MRI scans.
7. Investigation the presence of gene variants such as MUC2, encoding Mucin protein, that are associated with gut permeability.
8. **DETAILS OF PRODUCT(S)**

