### Recruitment of healthy volunteers

A research team from the University of Nottingham has developed an MRI protocol to assess intestinal wall thickness to indicate gut permeability on healthy participants [17]. To validate this tool to be used on MASLD patients, our team will scan 15 healthy volunteers twice, at baseline and after 6 weeks, and then compare their results with MASLD patients’ results at baseline and after 6 weeks. Participants will be recruited through:

- Approaching healthy participants, with CAP<250 kpa<8kP by a FibroScan™ within the past 6 months, who previously participated in research studies where [name] was the CI and who have consented to be contacted for future research. Designated members of the study team will contact past research participants using contact details previously provided or obtained by the CI from patient records, to invite them to participate in this study.

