**Inclusion criteria for healthy participants who will have MRI scans:**

- Participants willing and able to give informed consent for participation in the study.
- Participants aged ≥18 years.
- participants with CAP<250 kpa<8kP by a FibroScan™ within the past 6 months.

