### Exclusion criteria for the main study

- Have allergy toward soya, milk or chocolate.
- Have allergy toward pectin.
- Participants on a vegan diet.
- Have eating disorders or difficulties or gastrointestinal conditions e.g. malabsorptive conditions such as coeliac, irritable bowel syndrome (IBS) or Inflammatory Bowel Disease (IBD) or gastroparesis.
- Have chronic malnutrition condition.
- History of major surgery which potentially limits participation or completion of the study.
- History of previous intestinal surgery known to affect food intake
- or digestive function, including bariatric surgery.
- Use of antibiotics, antifungal medications, probiotics or prebiotics 90 days before the start of the study.
- Are taking the following medications: immunosuppressants, amiodarone and/or perhexiline.
- Are currently following or anticipated to commence a specialised commercially available weight loss diet and/or program or concomitant use of any weight loss medication or herbal weight loss products.
- History of side effects towards probiotics or prebiotics.
- History or current psychiatric illness.
- History or current neurological condition (e.g. epilepsy).
- Participants with other liver abnormalities.
- Evidence of monogenic metabolism diseases such as Lysosomal acid lipase deficiency (LALD), Wilson disease, Hypobetalipoproteinemia, or inborn errors of metabolism.
- Have had a weight change exceeding 3 kg within 3 months.
- Uncontrolled diabetes, active malignancy, or chronic infections.
- Having symptoms of active infection.
- Excessive alcohol intake defined as self-reported intakes greater than 21 units per week in men, and 14 units per week in women.
- Participants who are pregnant, breast feeding or actively planning pregnancy will be excluded from the study.
- Participation in any other trial in the last 3 months.

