**MRI visit 1 and 2:**

If the participant consents to have MRI scans, then the study team will schedule a scan for them within the same day of baseline visit. Both MRI scans visits will be arranged at the Sir Peter Mansfield Imaging Centre (SPMIC). The participant will attend the visit fasted and provide the stool sample. The MRI research team will use Philips 3T MRI scanner. The team will firstly scan the hepatic fat and other surrounding GI organs fat using Dixon MRI sequences. Then, a medical doctor will cannulate the participant, take a blood sample from the participant and will ask them to drink the oral contrast which consists of 2.5% Mannitol and 0.2% Locust Bean Gum and will be prepared at the SPMIC on the morning of the scan. The participant will be asked to drink the oral contrast gradually over 40 minutes. This contrast required to provide contrast between the lining of the gut and its contents. After that, the medical doctor will prescribe and administer hyoscine butylbromide (Buscopan®) through the cannula while MRI research team taking T2* MRI measures of gut wall to measure gut permeability. Buscopan® is used to stop the bowel moving to allow the team to generate clear pictures of the bowel wall.

The medical doctor will confirm eligibility and document this, prior to performing any research activity related to the cannulation/administration of hyoscine butylbromide (Buscopan®).

Both MRI and baseline visit will take around 4 hours to complete all the research activities.

It is extremely unlikely that MRI scan will show any abnormality. Even if there were an abnormality, it is unlikely that research team would notice it since we are taking these MRI scans for scientific research, so they are not the same as scans collected by doctors for medical purposes. Furthermore, the pictures will not be looked at by a radiologist.

If the research team did find anything abnormal on the MRI scan, the investigator would arrange for an appropriately qualified doctor, from a healthcare provider e.g. a NHS Trust or a private doctor, to look at them. That specialist doctor would contact participant GP to explain the situation, so that participant GP could then advise them.

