**Dietary intervention (6 weeks):**

Control and intervention arms: Each participant will be randomly assigned to either pectin with whey protein and cocoa powder or control whey protein with cocoa powder using online software (sealedenvelope.com) to determine intervention A or B at enrolment. Randomisation will ensure equal distribution of key characteristics that might confound between-group comparisons and will be evaluated using baseline data analysis. Participants in the intervention arm (N=15) will be required to take 15g of pectin combined with 15g of unflavoured whey protein powder and 5g of cocoa powder as a flavour per day for a period of 6 weeks. The participants in the placebo/control arm (N=15) will be required to take 30g of unflavoured whey protein powder combined with 5g of cocoa powder as a flavour per day for the same period of 6 weeks. All supplements will be provided, pre-weighed, in food grade pouches and will be given sufficient cover the total intake for the 6-weeks period. Participants will be asked to incorporate the supplement provided in 250-300ml of water taken once at morning or evening. Regular weekly contact will be made via phone calls by [name] to record patients’ feedback or any adverse event that might occur due to ingestion of supplements and to ensure participants receive any information that becomes available during the course of the research that may be relevant to their continued participation .

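### The week-6 patient–volunteer MRI comparison mixes disease with supplement, volunteers are not screened for several gut conditions or recent antibiotics, and a T2* group difference alone is only weak validity evidence

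*Protocol*

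**What the plan says.** The Secondary Objectives include "Validation of MRI measures (T2*) as a tool to measure gut permeability among MASLD patients". The method is given in the Synopsis (Description of interventions) and under Recruitment of healthy volunteers: "To validate this tool to be used on MASLD patients, our team will scan 15 healthy volunteers twice", at baseline and six weeks later, "and then compare their results with MASLD participant results at baseline and after 6 weeks".

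For patients who agree to MRI, "the study team will schedule a scan for them within the same day of baseline visit" (MRI visit 1 and 2). They then take pectin with whey, or whey alone, "per day for a period of 6 weeks" (Dietary intervention), and are scanned again at the end.

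Volunteers must consent, be adults and meet a FibroScan criterion: "participants with CAP<250 kpa<8kP by a FibroScan" within six months. Their only exclusions are MRI contraindications, inability to tolerate the scan, and contraindications to Buscopan. The main-study list is longer. It bars gastrointestinal conditions, for example "malabsorptive conditions such as coeliac, irritable bowel syndrome (IBS) or Inflammatory Bowel Disease (IBD) or gastroparesis", as well as relevant intestinal surgery and antibiotic, antifungal, probiotic or prebiotic use in the preceding 90 days.

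**The concern.** A comparison of patients with healthy people supports T2* as a permeability measure only if the groups differ in permeability because of the disease and in little else that affects it. Two features of the plan weaken that.

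First, the week-6 contrast sets untreated volunteers against supplemented patients. The Project Rationale argues that low-methoxy pectin strengthens the gut barrier and lowers permeability. If so, the patient–volunteer gap narrows at week 6 for a reason unrelated to how well T2* works.

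Second, the Background section ties dysbiosis to increased permeability, yet recent antibiotics and several gut conditions are screened out in patients only.

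A third issue is separate and goes deeper: even a clean group difference in T2* does not show agreement with a measure of permeability. At stake is a stated secondary objective that uses 15 of the 45 participants, each attending two visits of about four hours with cannulation and an injection.

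**Working it through.** The protocol gives no figure to reproduce here: no sample-size reasoning, expected difference or SD for T2*. The check is a reading of the passages, followed by an illustration of size.

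**1. Timing.** The patients' first scan is on the baseline day, when they attend fasted and the supplement is first dispensed. That contrast precedes the course. The second scan follows the full course. Neither description of the volunteer comparison mentions arm.

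**2. Eligibility side by side.**

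| Condition | Patients | Volunteers |
|---|---|---|
| Ulcerative colitis | excluded (as IBD) | excluded (Buscopan list) |
| GI stenosis, ileus, reflux disease, hiatus hernia | excluded if having MRI | excluded (Buscopan list) |
| Coeliac disease, IBS, other IBD, gastroparesis | excluded | not excluded |
| Intestinal surgery affecting intake or digestion | excluded | not excluded |
| Antibiotics/probiotics within 90 days | excluded | not excluded |

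**3. Reference measure.** The Background section calls the lactulose-to-mannitol ratio the most widely used and validated permeability marker, but no visit collects it. Zonulin is a primary marker in patients, but no analysis pairing it with T2* is named. The efficacy section mentions correlation coefficients only in general terms. Volunteers give blood at the MRI visit with no assay stated.

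**4. Size (illustrative).** Assumptions: two-sided 0.05, normal approximation, equal SDs, 15 volunteers, m patients scanned, no effect of whey on T2*. MRI is optional, so m may be anything from 0 to 30.

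Standard error in SD units = √(1/15 + 1/m). Gap detectable with 80% power = (1.960 + 0.842) × SE.

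- m = 30: 2.802 × √0.1000 = 0.89 SD
- m = 15: 2.802 × √0.1333 = 1.02 SD
- m = 5: 2.802 × √0.2667 = 1.45 SD

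Suppose the arms are pooled 1:1 at week 6 and pectin closes a fraction f of the gap d in its arm. The pooled gap is d(1 − f/2), and power = Φ(gap/SE − 1.960), with SE = 0.316 for m = 30.

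| d (SD) | f | Pooled gap | Power |
|---|---|---|---|
| 1.0 | 0 (as at baseline) | 1.00 | 0.89 |
| 1.0 | 0.5 | 0.75 | 0.66 |
| 1.0 | 1 | 0.50 | 0.35 |
| 0.8 | 0 (as at baseline) | 0.80 | 0.72 |
| 0.8 | 0.5 | 0.60 | 0.48 |
| 0.8 | 1 | 0.40 | 0.24 |

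If c of the 15 volunteers have patient-like permeability, the gap becomes d(1 − c/15), at baseline as well. For c = 3, a gap of 1.0 becomes 0.80 (power 0.89 to 0.72) and 0.8 becomes 0.64 (0.72 to 0.53).

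**The case against.** The strongest reply is that the plan already contains the right comparison. Patients are scanned before supplementation, so the baseline contrast with volunteers carries no treatment effect. This stands. A reader might infer that the whole validation depends on the treatment effect; that is true only of the week-6 half.

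Nor does the protocol say that arms are pooled at week 6. Its general methods analyse by group and time, and the handling of arm could sit in an analysis plan that is not shown. Read by arm, a shift in T2* under pectin could even be evidence of responsiveness. This also stands, so the power losses in the table are conditional on pooling.

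A reader might infer that anyone with gut disease can count as healthy. The Buscopan list rules that out for ulcerative colitis, stenosis, ileus, reflux disease and hiatus hernia. The protocol also says it will approach healthy people from earlier studies, and nothing suggests how many with the remaining conditions would enrol. The word healthy is not an eligibility criterion, however, so the gap for those conditions remains.

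Finally, the Background section reports that T2* was validated in healthy volunteers and that MASLD patients have higher permeability. Comparing groups expected to differ is a recognised, if weak, form of validity evidence, and the loosely worded correlation plan could cover T2* and zonulin. It would therefore be too strong to say that nothing links T2* to permeability. The previous validation was not in MASLD, though, and no specific pairing is stated.

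**Conclusion.** The point holds in limited form. The week-6 patient–volunteer contrast confounds disease with supplement and has no stated rule for arm. The volunteer criteria omit several exclusions applied to patients that bear on permeability. Both choices are fixed by the protocol: which scans are compared for validation, and who may be scanned.

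The documents do not support the inference that these two faults are why validation fails. Curing both would leave a clean known-groups contrast that is still only weak evidence, because no reference permeability test is collected and no T2*–zonulin analysis is named. That absence is the main limit on the objective as worded.

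The size rests on assumed gaps of 0.8 to 1.0 SD, full MRI uptake and pooled arms. With lower uptake, even the baseline contrast can detect only gaps of 1 SD or more.

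The label also varies: the Synopsis and the volunteer recruitment section speak of intestinal wall thickness, while the objectives, endpoints and scan procedures speak of T2*. This is minor. The primary outcome and the randomised comparison of T2* between arms are not affected.

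**What to change.** - Base the patient–volunteer T2* contrast on baseline scans only.
- Analyse patients' week-6 scans by randomised arm, and use the volunteers' second scan for repeatability (within-person SD).
- Extend the main-study exclusions for gut disease, intestinal surgery and 90-day antibiotic/probiotic use to volunteers.
- Describe the objective as an exploratory known-groups comparison, not validation, and support it with a pre-stated baseline T2*–zonulin correlation in patients. That correlation would be supportive only. With 30 patients, 80% power needs r of about tanh(2.802/√27) = tanh(0.539) = 0.49; with 15, about tanh(2.802/√12) = tanh(0.809) = 0.67.
- Replace intestinal wall thickness with T2* in the Synopsis and in Recruitment of healthy volunteers.

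The cost is a protocol amendment, with ethics approval where required, and slightly slower recruitment of 15 volunteers. No visit or scan is added. The eligibility change helps only if made before volunteers are enrolled.

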# ABBREVIATIONS

AASLD American Association for the Study of Liver Disease

AE Adverse Event

ALP Alkaline Phosphatase

ALT Alanine Aminotransferase

AST Aspartate Aminotransferase

CAP Controlled attenuation parameter

CI Chief Investigator overall

CRF Case Report Form

CT Computerized tomography

DILI Drug-Induced Liver Injury

DMC Data Monitoring Committee

ELF Enhanced Liver Fibrosis

GABA gamma-aminobutyric acid

GCP Good Clinical Practice

GGT gamma-glutamyl transferase

GSRS Gastrointestinal Symptom Rating Scale

HADS Hospital Anxiety and Depression Scale

HBA1C Haemoglobin A1C

HCV Hepatitis C Virus

HM High methoxyl

HPA hypothalamic-pituitary-adrenal

IBD Inflammatory bowel disease

IBS Irritable bowel syndrome

ICF Informed Consent Form

IQR Interquartile ranges

LALD Lysosomal Acid Lipase Deficiency (LALD)

LM Low methoxyl

MASH Metabolic Dysfunction-associated Steatohepatitis

MASLD Metabolic dysfunction-associated steatotic liver disease

MRI Magnetic resonance imaging

NAFLD Non-alcoholic fatty liver disease

NASH Non-alcohol related steatohepatitis

NHS National Health Service

NICE National Institute for Health and Care Excellence

PI Principal Investigator at a local centre

PIS Participant Information Sheet

QOL Quality of life

REC Research Ethics Committee

R&D Research and Development department

SAE Serious Adverse Event

SD Standard deviation

SLD steatotic liver disease

SPMIC Sir Peter Mansfield Imaging Centre

VTCE Vibration-controlled transient elastography

# TRIAL / STUDY BACKGROUND INFORMATION AND RATIONALE

**Metabolic Dysfunction-Associated Steatotic Liver Disease (MASLD): Definition and Prevalence**

Metabolic dysfunction-associated steatotic liver disease (MASLD), formerly known as non-alcoholic fatty liver disease (NAFLD), is the main cause of chronic liver disease and affects more than 32% adults globally. Meta-analysis studies across the world showed that the predicted incidence of MASLD is 47 cases per 1000 people with higher incidence in obese and overweight males [2]. Moreover, in the UK, this disease is affecting 1 in 5 people and is the most common liver disorder. The number of new cases is increasing, and it is estimated that MASLD/NAFLD will become the main reason for liver transplantation within the coming years [3, 4].

NAFLD- is defined as an accumulation of fat within the liver cells (steatosis), where the presence of fat is more 5% in the hepatic cells, and in the absence of other liver disease causes or significant alcohol intake. Significant alcohol consumption is defined by American Association for the Study of Liver Disease (AASLD) as recent or current alcohol use of >21 drinks/week in men and >14 drinks/week in women [5].

NAFLD includes a range of liver-related abnormalities. While most patients have simple steatosis, a smaller group of these patients can develop non-alcoholic steatohepatitis (NASH), a more progressive form of liver disease that is defined as the presence of hepatic steatosis with evidence for liver cell injury (apotosis) and characterised by inflammation and fibrosis. In later stages, NASH can progress to ongoing hepatic fibrosis, then to cirrhosis and can lead to life-threatening conditions including liver cancer and liver failure [6, 7].

MASLD as a terminology has been recently introduced by AASLD in June 2023 to replace NAFLD to accurately capture the cause of liver steatosis. Based on the new guidelines, patients will be diagnosed with MASLD if they have liver steatosis and have at least one of five cardiometabolic risk factors: obesity (BMI ≥25kg/ m2 (23 in Asians) or waist circumference >94cm in male, >80cm in female or ethnicity adjusted), insulin resistance (fasting serum glucose ≥ 5.6 mmol/l (100 mg/dl) or 2-hour post-load glucose levels ≥ 7.8 mmol/l (≥ 140 mg/dl) or HbA1c ≥ 5.7% (39 mmol/l) or type 2 diabetes or treatment for type 2 diabetes), hypertension (blood pressure ≥ 130/85 mmHg or specific antihypertensive drug treatment) and dyslipidaemia (plasma triglycerides ≥ 1.70 mmol/l (150 mg/dl) or lipid-lowering treatment or plasma HDL-cholesterol ≤ 1.0 mmol/l (40 mg/dl) (male) and ≤ 1.3 mmol/l (50 mg/dl) (female) or lipid-lowering treatment. NASH has been also replaced by Metabolic dysfunction-associated steatohepatitis (MASH) to indicate that steatohepatitis is related to metabolic dysfunction. Moreover, an overarching term of steatotic liver disease (SLD) was introduced by AASLD to cover the different causes of liver steatosis and a new category, separate from MASLD, called MetALD was introduced to classify individuals with MASLD who consume higher weekly amounts of alcohol—specifically over 140 grams (14 drinks) for females and 210 grams (21 drinks) for males [8, 9]. These subtypes are shown in Figure 1

[figure not shown]

Figure 1: Reproduced from [9]

